## Abstract

**Background:**

Proteinuria after kidney transplantation (KTx) has been a frequent problem due to several factors, high protein intake being one of them. Individualized nutritional intervention in the late post-KTx period can promote the improvement or the reduction of risks associated with the parameters of evaluation of kidney function, body composition, and quality of life in individuals submitted to KTx.

**Methods:**

This is a single-center, randomized and stratified clinical trial. The study will be conducted in a university hospital in northeastern Brazil with 174 individuals aged ≥19 years submitted to KTx and followed up for 12 months. Assessments will take place at 3-month intervals (T0, T3, T6, T9, and T12). The patients will be allocated to intervention and control groups by random allocation. The intervention group will receive individualized nutritional interventions with normoproteic diets (1.0 g/kg) after 60 days of KTx whereas the controls will receive the standard nutritional guidance for the post-KTx period. The primary efficacy variable is the change from baseline in log proteinuria assessed with the urinary albumin/creatinine ratio. Secondary efficacy variables include body composition, anthropometry, quality of life assessment and physical activity, lipid profile and glycemic control. Ninety-two subjects per group will afford 70% power to detect a difference of 25% between groups in log proteinuria. Primary efficacy analysis will be on the modified intention-to-treat population with between-groups comparison of the change from baseline in log proteinuria by analysis of covariance.

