### Sample size and recruitment

The sample calculation was performed using the software Stata 15.1 (Stata Corp., College Station, TX), based on a published study of patients who had undergone KTx with a mean log proteinuria of 2.36 mg (standard deviation of 1.55) at 6 months, by the urinary albumin/creatinine ratio [17]. To demonstrate a difference of 25% in the geometric mean of proteinuria at 6 months between the trial groups, with α error of 5% (α ≤ 0.05) and statistical power of 70%, 87 patients per study group will be needed. Assuming a drop-out rate of 5% prior to the first follow-up visit, the sample size is set at 92 subjects per group. Recruitment is scheduled to take place from May 1, 2019 through to December 31, 2022.

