### Statistical analysis

The study will be analyzed by the modified intention-to-treat method, whereby all randomized patients who had at least one post-baseline measurement of proteinuria will be included in the primary analysis population. Data will be presented descriptively by means and standard deviations, or with absolute and relative frequencies, according to the respective scale of measurement. The difference between the groups in the change from baseline in the primary efficacy variable will be tested by analysis of covariance with a multiple linear regression model, with the baseline value entered as covariate, *Diabetes mellitus* entered as stratification variable, and study group as independent variable. For secondary efficacy variables, in those measured in an interval scale, the change from baseline will be compared between groups with the same method. For those variables that are related to patient sex (e.g., WC, sarcopenia), sex will be included as independent variable. For variables measured in ordinal scales, only the values observed in the last valid observation will be considered and will be compared between groups with the Wilcoxon-Mann-Whitney U test. No multiplicity correction of p-values will be applied to the secondary variables.

Statistical analyses will be performed using Stata 15.1 (Stata Corp., Collegue Station, TX). Tests with two-sided p values < 0.05 will be considered statistically significant.

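### The abstract gives the trial size as 174 individuals and also as 92 per group (184); 174 is the total before the dropout allowance and is the wrong figure for the number to be randomised

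*Protocol article*

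**What the plan says.** The Methods paragraph of the abstract gives two sizes. The study will be conducted "with 174 individuals aged ≥19 years submitted to KTx and followed up for 12 months". Further on, "Ninety-two subjects per group will afford 70% power to detect a difference of 25% between groups in log proteinuria".

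The section Sample size and recruitment derives the number. It starts from a published study with a "mean log proteinuria of 2.36 mg (standard deviation of 1.55) at 6 months" and sets its aim: "To demonstrate a difference of 25% in the geometric mean of proteinuria at 6 months between the trial groups". It concludes, "with α error of 5% (α ≤ 0.05) and statistical power of 70%, 87 patients per study group will be needed". It then assumes that 5% will drop out before the first follow-up visit, and so "the sample size is set at 92 subjects per group".

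The section Statistical analysis defines a modified intention-to-treat population. A randomised patient enters the primary analysis only with a proteinuria value after baseline. The test is an analysis of covariance with the baseline value and diabetes in the model. On sidedness: "Tests with two-sided p values < 0.05 will be considered statistically significant".

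**The concern.** Both figures stand in one paragraph, and neither is labelled as randomised, evaluable or followed up. A reader who takes the first figure as the number to be enrolled gets 174. A reader who doubles the second gets 184.

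The difference is exactly the dropout allowance. A patient lost before any post-baseline proteinuria measurement leaves the primary analysis, so the allowance protects the analysed sample. Planned power is only 70%, so there is little margin. The achieved sample will also be compared with the abstract when the trial is reported: with 174 randomised, the trial would be complete by one sentence and ten short by the other.

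**Working it through.** **Inputs.** From Sample size and recruitment: mean log proteinuria 2.36, SD 1.55, alpha 5%, power 70%, 87 per group, 5% dropout, 92 per group. From Statistical analysis: two-sided tests. From the abstract: 174 in total, 92 per group. Equal allocation is implied by the equal group sizes.

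**1. Reproducing 87 per group.** The plan does not print the log difference it used. Taking 25% of the log mean gives 0.25 × 2.36 = 0.59, and a standardised difference of 0.59/1.55 = 0.3806.

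- Normal approximation: n = 2 × (1.960 + 0.524)² × 1.55²/0.59² = 85.2, rounded up to 86 per group.
- t-based calculation: 86.17, rounded up to 87 per group.
- One-sided version: 65 to 66 per group, which does not match.

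So 87 is reproduced with a two-sided t-test and a difference of 0.59. That difference is an inference from the match.

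**2. Reproducing 92 per group.** 87/0.95 = 91.6, rounded up to 92. (Multiplying instead, 87 × 1.05 = 91.4, also rounds up to 92.)

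**3. The two totals.**

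| | Per group | Total |
|---|---|---|
| Needed before the dropout allowance | 87 | 174 |
| Set as the sample size | 92 | 184 |

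The difference is 10 patients. The abstract's 174 is exactly 2 × 87. The calculation in the methods section is sound on these inputs; the fault lies in which total was carried into the abstract.

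**4. Expected number analysed after 5% early loss.**

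- 184 randomised: 184 × 0.95 = 174.8, about 87 per group.
- 174 randomised: 174 × 0.95 = 165.3, about 82 to 83 per group.

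**5. Power in an unadjusted two-sided t-test (difference 0.59, SD 1.55).**

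| Analysed | Power |
|---|---|
| 92 + 92 | 72.8% |
| 87 + 87 | 70.4% |
| 83 + 82 | 68.1% |

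Randomising 174 in place of 184, with the plan's own 5% loss, moves power from 70.4% to 68.1%, a loss of 2.3 points. The 70% belongs to 87 analysed per group. If all 92 per group were analysed, power would be about 73%, so the abstract's pairing of 92 with 70% holds only once the dropout is understood.

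**The case against.** **The two totals can be reconciled as followed-up versus randomised.** The sentence with 174 speaks of 12 months of follow-up, and 184 less 5% is about 174. This is the best reading in the plan's favour, but it does not hold. The abstract does not label 174 as a subset of a larger number. The 5% covers only loss before the first follow-up visit, so 174 is the number expected to have some post-baseline value; the number still followed at 12 months would be lower if anyone left later.

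**The operative number is already fixed.** This stands. Sample size and recruitment sets 92 per group, and the abstract repeats it. A reader might infer that an unblinded trial with two totals has an open stopping point. The documents do not support that: the methods section gives one number, recruitment has calendar limits (May 1, 2019 to December 31, 2022), no data-dependent stop is described, and nothing says that recruitment ends at 174. A reader might also infer that the registry entry is wrong, but no registry target is shown.

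**The power loss is small and conditional.** This also stands. It arises only if 174 were the number randomised, and it ignores the baseline covariate. The document gives no correlation between baseline and follow-up. If it were assumed to be 0.21, 82.5 per group would be worth 82.5/(1 − 0.21²) = 86.3, against the 86.17 needed, which already restores 70%.

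**The 0.59 is not the stated effect.** The stated effect is a 25% difference in geometric means. If the logs are natural (an assumption), a 25% reduction is a log difference of −ln 0.75 = 0.288, and power is about 22% to 24% anywhere between 82 and 92 per group (normal approximation). On that reading the choice between 174 and 184 hardly matters. Whether the effect was specified correctly is a separate question, and the contradiction between the totals does not depend on it.

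**Conclusion.** The abstract's 174 is the wrong total for the number to be randomised. The protocol's own calculation makes it the requirement before dropout and sets the size at 92 per group, 184 in total. This conclusion needs only the printed figures and two equal groups.

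The size is ten patients. If 174 were randomised with 5% early loss, about 165 would be analysed, and power would be about 68% in place of about 70%. That power figure rests on an unadjusted t-test and on the inferred difference of 0.59.

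A reader might go further and conclude that the trial as planned misses its stated power. The documents do not support this: 92 per group with 5% loss leaves about 87 per group, which gives the planned 70% on the plan's apparent inputs, and even 174 randomised would give it if nobody were lost. This is a sample-size figure to correct in the abstract. It is no evidence that the trial will be under-recruited.

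**What to change.** In the abstract, replace the total of 174 with wording such as: *184 individuals (92 per group), expected to leave about 174 (87 per group) with a post-baseline measurement after 5% early dropout*. Attach the power statement to 87 per group, as Sample size and recruitment does.

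This only brings the abstract into line with the methods section. It does not endorse the 70% under the stated 25% difference in geometric means, which should be examined separately.

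The cost is one number and one clause in the abstract. The sample size, analysis population and tests do not change.

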**Discussion:**

The study will assess the effects of an individualized nutritional intervention on proteinuria 12 months after KTx.

**Trial registration:**

REBEC (RBR-8XBQK5).

## Introduction

Nutritional interventions in all stages of kidney transplantation (KTx) play important roles in individual care and in preventing common comorbidities that may arise in the post-KTx period, such as obesity or malnutrition, hypertension, diabetes, cardiovascular diseases [1], and clinical conditions such as proteinuria [2].

Proteinuria is an indicator of kidney function and, when present, it is associated with a higher incidence of acute rejection, hypertension, graft dysfunction, cardiovascular risk, and long-term mortality [3, 4]. This clinical condition may be due to several factors, such as the nephrotoxicity of immunosuppressive therapy, recurrent glomerulonephritis, glomerulopathies, ischemic damage from surgery, diabetic or hypertensive nephropathy, presence of native kidneys, and other indirect factors such as high sodium and protein intakes in the diet [2].

Although this perception exists, there are few studies that have assessed the impact of dietary protein in the late post-KTx period (> 6th week after surgery), making it difficult to construct guidelines for dietary recommendations for the nutritional management of these patients based on scientific evidence [5, 6]. Currently, only generalized nutritional guidelines are known that focus on preventing complications after KTx [7, 8]. Studies that consider nutritional interventions are still limited and inconclusive, mainly because they do not suggest evidence of long-term results [6, 9].

In the immediate post-KTx period (< 6th week after surgery), a high-protein (1.3 to 2.0 g/kg/day) and hypercaloric (30 to 35 kcal/kg/day) diet should be recommended to meet the needs caused by the resultant metabolic stress after surgery and the use of high doses of immunosuppressive therapy [10]. However, in the late post-KTx period, the characteristics of the diet are changed to normoproteic (1.0 g/kg/day) and normocaloric (25 to 30 kcal/kg/day) in order to meet the individual needs of each patient [11]. In addition, the choice of foods to be recommended is conditioned to the risks of non-surgical complications, requiring strict control over blood pressure, lipid and glycemic profile, weight gain, and the influence that these variables have on patients’ quality of life [6, 8, 10, 12].

The average weight gain after the first year of surgery is close to 5–10 kg or 5%–10% of the initial body weight [13, 14]. Likewise, the body composition analysis shows a higher percentage of adiposity in relation to lean mass, which is associated with obesity and other factors [15], and may suggest a negative influence on kidney function, especially in the success of the graft [20]. In addition to immunosuppressive therapy, increased appetite, change in lifestyle and reduced dietary restrictions as well as reversal of uremia and limited physical activity contribute to this scenario [13].

The patient’s quality of life and renal graft survival depend directly on post-KTx clinical care. Multiprofessional follow-ups help in the maintenance and early identification of abnormalities or signs of kidney function regression. Possibly, adequate intake of energy and protein in the diet could contribute to control lipid levels and to maintain the balance of micronutrients such as sodium, calcium, iron, potassium and phosphorus in the late post-KTx period that favors the maintenance of kidney function, especially in the reduction or prevention of proteinuria, decreasing the risk of complications, helping to maintain a favorable body composition, and improving the quality of life of patients undergoing KTx [1, 2, 6, 10].

Considering the scarcity of nutritional guidelines and the heterogeneity of experimental studies on dietary recommendations after KTx, this study aimed to evaluate the effect of an individualized nutritional intervention on the parameters of assessment of kidney function, body composition, and quality of life in individuals submitted to KTx followed for 12 months in a nephrology clinic at an university hospital in northeastern Brazil.

## Materials and methods

This is a single center, stratified and randomized clinical trial to evaluate the efficacy of individualized nutritional intervention considering normal protein diet with consumption of 1.0 g/kg versus standard nutritional guidelines in chronic kidney disease patients submitted to KTx in the previous two months. The trial site will be the Onofre Lopes University Hospital/Federal University of Rio Grande do Norte (UFRN), Rio Grande do Norte, Brazil.

The study was submitted to and approved by the Research Ethics Committee of Onofre Lopes University Hospital/UFRN with authorization number 3,127,266 and registered with the CAAE: 02445018.7.0000.5292. Eligible patients will be informed verbally and in written about the objectives, procedures and potential risks of the study. Those agreeing to participate will be asked to sign an informed consent form. The clinical trial was registered on the *Brazilian Clinical Trials Registry (REBEC)* online platform, obtaining the registration RBR-8XBQK5 and UTN (*Universal Trial Number*) U1111-1231-6000, linked to the World Health Organization (WHO).

### Trial design

The clinical trial groups will be evaluated at Time 0 (T0) or immediate post-KTX and every three months thereafter, until to complete 12-months post-KTx. At each study visit, the patients will be evaluated for kidney function and other biochemical parameters, food consumption, anthropometric measurements, body composition, and quality of life, as shown in Fig 1. Fig 2 depicts the study diagram according to the Standard Protocol Items: Recommendations for Interventional Trials–SPIRIT [16].

**Fig 1 pone.0272484.g001:**
[figure not shown]
Flowchart in months with the design of the study from the recruitment of patients to data collection, considering the time of transplantation. DXA, *double-beam X-ray absorptiometry*; SF-36, *Medical Outcomes Study 36-Item Short-Form Health Survey*; SRQ-20, *Self-Reporting Questionnaire*; IPAQ, *International Physical Activity Questionnaire*.

**Fig 2 pone.0272484.g002:**
[figure not shown]
SPIRIT diagram. *Time-points of the protocol: -T0, enrolment; T0, baseline; T60, 60th day after transplant; T3, month 3; T6, month 6; T9, month 9; T12, month 12. DXA, *double-beam X-ray absorptiometry*; SF-36, *Medical Outcomes Study 36-Item Short-Form Health Survey*; SRQ-20, *Self-Reporting Questionnaire*; IPAQ, *International Physical Activity Questionnaire*.

### Inclusion and exclusion criteria

The study will include individuals of both sexes aged 19 years and older who underwent KTx in the previous two months, with exclusively on oral feeding, and be literate or have a literate caregiver. The exclusion criteria will be patients with diagnosis of focal segmental glomerulosclerosis, systemic lupus erythematosus, IgA nephropathy, with multiple organ transplantation, with a history of recurrent transplantation due to chronic rejection, patients on immunosuppressive therapy of everolimus or sirolimus, and with hospital stay longer than 60 days after surgery.

### Primary and secondary efficacy variables

The primary and secondary efficacy variables defined for the study are described in Table 1.

**Table 1 pone.0272484.t001:** Description of the primary and secondary efficacy variables for patients who have received a KTx and participated in the study.

Primary efficacy variable	Secondary efficacy variable
**• Change from baseline in log proteinuria (urinary albumin/creatinine ratio)**	• Change from baseline in the body adiposity percentage
	• Change from baseline in lean body mass
	• Change from baseline in body mass index
	• Difference in quality of life and physical activity
	• Change from baseline in lipid profile (triglycerides, total cholesterol, high-density lipoprotein cholesterol and low-density lipoprotein cholesterol)
	• Change from baseline of glycemic control (fasting glucose and glycated hemoglobin).

### Sample size and recruitment

The sample calculation was performed using the software Stata 15.1 (Stata Corp., College Station, TX), based on a published study of patients who had undergone KTx with a mean log proteinuria of 2.36 mg (standard deviation of 1.55) at 6 months, by the urinary albumin/creatinine ratio [17]. To demonstrate a difference of 25% in the geometric mean of proteinuria at 6 months between the trial groups, with α error of 5% (α ≤ 0.05) and statistical power of 70%, 87 patients per study group will be needed. Assuming a drop-out rate of 5% prior to the first follow-up visit, the sample size is set at 92 subjects per group. Recruitment is scheduled to take place from May 1, 2019 through to December 31, 2022.

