## Discussion

The main clinical relevance of this randomized trial is to provide information on the impact of an individualized nutrition intervention with a defined amount of protein intake on the 25% reduction in proteinuria levels in the late post-KTx period. In addition, this study will allow to evaluate other relevant parameters related to metabolic and quality of life outcomes, since this study raises the hypothesis that this balanced diet may improve parameters of body composition, lipid and glucose profiles, as well as quality of life of patients in the post-KTx.

Patients with KTx in the present clinical trial will undergo an individualized nutritional intervention for 12 months after surgery. This period of nutritional intervention was selected based on previous studies, which demonstrated that protein intake is associated with maintenance of kidney function in the first year post-KTx [30–32]. However, studies on the assessment of the impact of dietary protein intake in post-KTx patients remain scarce and controversial [33–36].

A study conducted by Deetman et al. [33], including patients with more than 6-months post-KTx, identified that a higher protein intake would have a protective effect against renal graft failure. Another study in patients with 1 year of KTx, also suggested that the restriction of protein intake should not be advised after KTx, as low protein intake would be associated with an increased risk of mortality and graft failure [34]. Other studies that evaluated the impact of dietary intervention on the post-KTx also showed conflicting results, mainly due to limitations in their methodological designs [35, 36].

Thus, due to the lack of data with high quality of evidence on the influence of dietary intervention on post-KTx, there are no guidelines or recommendations for a specific nutritional intervention in the late post-KTx period [37]. In addition, in post-KTx, there is insufficient evidence to recommend a particular protein type (plant vs animal) in terms of the effects on nutritional status or the blood lipid profile [8].

The primary efficacy variable evaluated will be proteinuria as it is a recognized marker of kidney injury [4, 38]. Post-KTx proteinuria is associated with worse outcomes, being a strong risk factor in predicting graft survival and mortality [4]. Fernández-Fresnedo [39] also demonstrated that proteinuria at 1 year after KTx is an excellent marker of poor long-term graft prognosis.

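### The 87 per group rests on 25% of the mean log proteinuria (0.59 log units), not a 25% difference in geometric means; power for the stated effect is about 23% (natural log, unadjusted), not 70%

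*Protocol article*

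**What the plan says.** The section Sample size and recruitment takes its planning values from a published transplant cohort: "mean log proteinuria of 2.36 mg (standard deviation of 1.55) at 6 months", measured by the urinary albumin/creatinine ratio. The base of the logarithm is not given. The target is worded as "To demonstrate a difference of 25% in the geometric mean of proteinuria at 6 months between the trial groups", and the result as "statistical power of 70%, 87 patients per study group will be needed". An allowance of 5% for drop-out raises this to 92 per group.

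The Abstract words the effect differently: "Ninety-two subjects per group will afford 70% power to detect a difference of 25% between groups in log proteinuria". The Discussion describes the trial's main relevance as information "on the 25% reduction in proteinuria levels in the late post-KTx period".

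The Statistical analysis section makes tests two-sided ("Tests with two-sided p values < 0.05 will be considered statistically significant"). It plans analysis of covariance of the change in log proteinuria, with the baseline value as covariate and diabetes as stratification variable.

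**The concern.** The sample size section speaks of 25% in the geometric mean, the Abstract of 25% in log proteinuria. These are two different quantities, yet both carry the same 70% power. On the log scale a percentage difference between geometric means is a fixed shift that does not depend on the mean. A percentage of the log mean is not a usable effect size, because it changes with the unit in which the ratio is expressed, while the data and their SD on the log scale do not.

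This is the primary endpoint, and the calculation is the only justification of the sample size. If 87 was obtained from 25% of the log mean, the trial has far less chance of detecting a 25% reduction than a reader is told. A non-significant result could then be taken as evidence against an effect that the trial was unlikely to find.

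**Working it through.** **Inputs.** From Sample size and recruitment: mean of logs 2.36, SD 1.55, α = 0.05, power 70%, equal groups, 5% drop-out. From Statistical analysis: two-sided tests.

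**Formula.** Normal approximation for two means: n per group = 2 × (1.960 + 0.524)² × (SD/δ)² ≈ 12.34 × (SD/δ)². The two-sample t-test version uses the noncentral t distribution and gives about one patient more.

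**1. Reproducing 87.** Take δ = 0.25 × 2.36 = 0.59.
- Normal approximation: 12.34 × (1.55/0.59)² = 85.2, so 86.
- t-test: 86.2, so **87**, with power 70.4%.
- Drop-out: 87/0.95 = 91.6, so **92**.

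Both stated figures are matched exactly.

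**2. The effect as worded in the sample size section.** A geometric mean lower by 25% means δ = |ln 0.75| = 0.288 (natural log) or |log10 0.75| = 0.125. A geometric mean higher by 25% means δ = ln 1.25 = 0.223 or log10 1.25 = 0.097. With SD 1.55, two-sided 5%, t-test:

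| Effect | δ | n per group for 70% | Power at 87 per group |
|---|---|---|---|
| 25% of the log mean | 0.590 | 87 | 70% |
| 25% lower, natural log | 0.288 | 360 | 23% |
| 25% higher, natural log | 0.223 | 597 | 16% |
| 25% lower, log10 | 0.125 | 1,901 | 8% |
| 25% higher, log10 | 0.097 | 3,159 | 7% |

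Check of the second row by the normal approximation: standard error = 1.55 × √(2/87) = 0.235; 0.288/0.235 = 1.224; power = Φ(1.224 − 1.960) = 0.231. With all 92 per group, power is 24%. One-sided testing, which the plan does not use, would still need 274 per group for a 25% reduction on the natural log scale. No reading of 25% in the geometric mean returns 87.

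**3. What 0.59 log units means.** With natural logs, exp(−0.59) = 0.55, a 45% reduction. With log10, 10^(−0.59) = 0.26, a 74% reduction.

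**4. Dependence on the unit.** Suppose the ratio were expressed in a unit ten times smaller. On the natural log scale the mean would become 2.36 + ln 10 = 2.36 + 2.303 = 4.663, and 25% of it 1.166. The SD stays at 1.55. Then n = 12.34 × (1.55/1.166)² ≈ 22 per group, for the same patients and the same treatment effect.

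**5. Baseline adjustment.** Analysis of covariance reduces the SD to 1.55 × √(1 − ρ²), where ρ is the correlation between baseline and follow-up. The protocol gives no ρ, so a range is assumed. For a 25% reduction, natural log, 87 per group:

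| Assumed ρ | Residual SD | Power |
|---|---|---|
| 0 | 1.55 | 23% |
| 0.3 | 1.48 | 25% |
| 0.5 | 1.34 | 29% |
| 0.6 | 1.24 | 33% |
| 0.7 | 1.11 | 40% |
| 0.8 | 0.93 | 53% |

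Reaching 70% takes a residual SD of 0.76, that is ρ = √(1 − (0.764/1.55)²) ≈ 0.87.

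**The case against.** The best defence is that the calculation agrees with the Abstract, which speaks of 25% in log proteinuria, and that log proteinuria is the primary variable. On that reading the sample size section is mislabelled rather than miscalculated. This explains how the figure arose, but the power claim still fails: the section that justifies the number names the geometric mean, the Discussion speaks of a 25% reduction in proteinuria, and a percentage of a log mean has no fixed meaning.

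The figure of 23% is also conditional. It assumes natural logs, a reduction rather than an increase, and no covariate adjustment, while the plan does adjust for baseline. That is fair, and the conditions should be stated with the figure. They do not rescue the claim. Base 10 or an increase makes power lower. Adjustment makes it higher, but the calculation did not use it, since the unadjusted SD already returns 87. Nothing in the protocol supports a correlation near 0.87 between a baseline taken immediately after transplantation and follow-up months later.

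The preference for natural logs is a judgement, because the source study is not at hand; an SD of 1.55 on log10 would be extreme. How a null result would be read is likewise a prediction.

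Finally, rewording the effect to suit the existing sample size does not show that a 45% reduction is plausible. This stands, and the corrected text should not imply that it does.

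**Conclusion.** The concern holds. The stated 87 per group (92 with drop-out) corresponds to a difference of 0.59 in mean log proteinuria, which is 25% of 2.36, and not to a 25% difference in geometric means. On natural logs the trial has 70% power for a reduction of about 45%. For a 25% reduction its power is about 23% unadjusted, so it would miss such an effect roughly three times in four. At assumed baseline correlations of 0.5 to 0.7 power is 29% to 40%. On base-10 logs the unadjusted power is about 8%.

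The mismatch itself needs no assumption beyond the protocol's own inputs. Only the size of the shortfall depends on the log base, the direction of the effect and the baseline correlation. The claim of 70% power has to be corrected.

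**What to change.** - In Sample size and recruitment, state the log base and say that 87 evaluable patients per group give 70% power, two-sided 5%, for a difference of 0.59 in mean log albumin/creatinine ratio. If the logs are natural, add that this is a geometric mean ratio of about 0.55, a reduction of about 45%.
- State there that power for a 25% reduction is about 23% without baseline adjustment. If credit is taken for the analysis of covariance, give the assumed baseline correlation and its source.
- Bring the Abstract and the Discussion into line. A 25% reduction may remain as the effect of interest, but not as the effect the trial is powered to detect.
- Report the primary result as a geometric mean ratio with its 95% confidence interval, and do not read non-significance as absence of a 25% effect.

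The cost is a text correction and a less favourable stated detectable effect; no patients are added. The alternative, powering for a true 25% reduction without adjustment on natural logs, would take about 360 evaluable patients per group, or 360/0.95 ≈ 379 with drop-out, against the 92 planned.
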